##### 4.n.1. *Expected treatment effect*

The objective of the current study is to assess whether mifepristone 600 mg is potentially effective for PTSD population. Currently, no published studies have examined mifepristone for the treatment of PTSD; however, other major drug studies in PTSD have defined responder status as a 30% reduction in CAPS score. Brady et al. performed a large multisite 12 week, double-blind, placebo-controlled trial to test the efficacy of sertraline; using conservative last observation carried forward, response rates were 53% for the drug group and 32% for placebo group (2000). Similarly, using the intent-to-treat principle, Davidson et al. reported response rates of 60% for the drug group and 38% for the placebo group (2001). The response rates of a double-blind, placebo-controlled pilot study of sertraline in military veterans with PTSD carried out by Zohar et al. were 41% for the drug group and 20% for the placebo group (2002). Marshall et al. evaluated the efficacy and safety of paroxetine for the treatment of patients with chronic PTSD; responder rates were 67% for the drug group and 37% for the placebo group (2001). A similar study carried out by Tucker et al. for paroxetine showed response rates of 58.8% and 38% for the drug and placebo group, respectively (2001). A large study of fluoxetine had response rates of 59.9% for the drug group and 43.8% for the placebo group (Martenyi et. al, 2002).

This study will use a 30% reduction in CAPS total score from baseline to four week follow-up to classify the participants as responders vs. non-responders. The proportion of responders to 600 mg mifepristone will be compared to the proportion of responders to placebo. The referenced studies report response rate differences ranging from 16% to 30% and placebo response rates ranging from 20% to 44%. In the present study, we will consider a 15% difference in the proportion of treatment vs. control group responders to be clinically relevant, as this is the minimum response rate difference in the referenced studies. Since the design of this study is more rigorous, a conservative estimate of the clinically relevant treatment effect is appropriate.

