##### 4.n.2. *Sample size determination*

As mentioned above, the sample size has been calculated to provide at least 90% probability that mifepristone 600 mg has been correctly identified as being superior to placebo if the population difference in response rate is at least 15%. Using the calculations provided by Simon et al. (1985) and accounting for a 20% attrition rate which has been reported in other drug studies using a similar population (Bartzokis et al., 2005), a total sample size of 90 is required, or 45 per treatment group. Since the sample size varies according to the responder rate (as well as the magnitude of the difference of interest), and the responder rate for placebo is unknown, we assume a placebo responder rate of 40%, which is at the high end of the studies referenced above. By contrast, in order to have a one-sided Type I error rate of 5% and 80% power to detect the 15% difference between two

groups using a traditional hypothesis testing framework, the study would require 274~344 participants when the placebo responder rate changes from 20% to 44%, after adjustment for a 20% withdrawal rate. If the true population difference in response rate is smaller than 15% (between 10~12%) and if we still consider it clinical significant, the proposed sample size (n=72 completers or 90 with 20% withdrawal rate) will still provide at least 80~85% probability of correctly identifying the superior group.

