Sensitivity Analysis of Missing Data- In the analyses mentioned above, missing data will be replaced using three additional procedures. The first procedure will entail the assumption of “worst case scenario” where the participants with missing data at week 4 will be deemed non-responders. This approach will provide a conservative test of treatment effects. In the second procedure, the last available information about the primary outcome, if available at week 1, will be used to impute the missing data at week 4 and if missing at both week 1 and 4, participants will be deemed non-responders. The third procedure involves the comparison on all participants whose CAPS score are obtained on week 4.

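### Coding every missing week-4 outcome as non-response in both arms is not a worst case for the between-arm difference, and the protocol's statement that it is conservative does not hold in general

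*Protocol*

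**What the plan says.** Protocol section 4.p.1 (Primary Outcome) bases the decision on whether the observed week-4 responder rate is at least 15 points higher on mifepristone than on placebo. Missing week-4 scores are handled in the primary analysis by multiple imputation within each treatment group.

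Three further procedures follow under the sensitivity analysis of missing data:

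- In the first, "participants with missing data at week 4 will be deemed non-responders". No distinction is made between the arms. The protocol presents this as the worst case and adds: "This approach will provide a conservative test of treatment effects".
- The second carries the week-1 response status forward, and codes non-response if week 1 is missing too.
- The third uses only participants with a week-4 CAPS score.

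Section 4.n.2 sets the size of the problem by "accounting for a 20% attrition rate which has been reported in other drug studies using a similar population". The result is that "a total sample size of 90 is required, or 45 per treatment group". Attrition is given overall; no figure is given by arm.

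**The concern.** Coding a missing outcome as failure is the worst case for one arm's own response rate. The trial's decision rests on a difference between two rates, and there the same coding works in opposite directions. Missing mifepristone participants coded as failures count against the drug; missing placebo participants coded as failures count for it. The net effect depends on how many are missing in each arm, so the direction cannot be promised in advance.

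The protocol itself gives a reason to expect dropout to matter. Section 4.g notes that delayed treatment adjustment in a placebo-controlled study could cause dropouts and harm interpretability. If dropout is sufficiently higher on placebo, a result could be reported as having survived a worst-case, conservative check that in fact moved it in the drug's favour. Since the choice about a Phase III trial rests on one observed difference without a hypothesis test, what the trial may claim about robustness carries weight.

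**Working it through.** **Inputs from the protocol**

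- Sample size: 45 per arm, and "n=72 completers or 90 with 20% withdrawal rate" (section 4.n.2), so 36 completers per arm.
- Placebo response: "we assume a placebo responder rate of 40%, which is at the high end of the studies referenced above" (section 4.n.2). Section 4.n.1 gives a range of 20% to 44% in the cited trials.
- Difference of interest: "we will consider a 15% difference in the proportion of treatment vs. control group responders to be clinically relevant" (section 4.n.1), hence 55% against 40%.
- Attrition: 20% overall. Every split by arm below is an assumption.

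**The plan's own figure.** The probability of correct selection is Φ(d / √[(pc(1−pc) + pt(1−pt))/n]). With pc = 0.40, pt = 0.55 and n = 36: Φ(0.15 / √[(0.24 + 0.2475)/36]) = 0.901. Then 36/0.80 = 45 per arm, 90 in total. The protocol's sample size reproduces, so these inputs are read as intended.

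**Expected result of the first procedure.** Let dt and dc be the missing fractions on mifepristone and placebo, with missingness unrelated to outcome. Then

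expected difference = pt(1−dt) − pc(1−dc).

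The shift from the complete-data difference is pc·dc − pt·dt. It is positive, so the procedure inflates the difference, when dc/dt > pt/pc. With no true effect that means any excess of placebo dropout. At 55% against 40% the ratio must exceed 0.55/0.40 = 1.375, which at 20% overall is about 16.8% missing on mifepristone and 23.2% on placebo.

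| Missing, mifepristone / placebo | No effect (40% / 40%) | True 15 points (55% / 40%) |
|---|---|---|
| 25% / 15% | −4 | +7.25 |
| 20% / 20% | 0 | +12.0 |
| 15% / 25% | +4 | +16.75 |
| 10% / 30% | +8 | +21.5 |

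For example, 10% / 30% with no effect: 0.40 × 0.90 − 0.40 × 0.70 = 0.36 − 0.28 = +0.08.

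**Chance of crossing 15 points with no true effect**, exact binomial, 45 per arm, 40% response in both. With complete data it is 8.1%. Fixed missing counts per arm give:

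| Missing, mifepristone / placebo | Non-responder coding crosses | Completers cross | Both cross |
|---|---|---|---|
| 9 / 9 | 5.9% | 9.3% | 5.9% |
| 7 / 11 | 11.9% | 10.2% | 10.2% |
| 5 / 13 | 21.4% | 10.3% | 10.3% |
| 13 / 5 | 0.9% | 10.4% | 0.9% |

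If the number missing is also allowed to vary at random, the first column becomes 14.4% at 15% / 25% and 25.6% at 10% / 30%. Hence the ranges of about 12–14% and 21–26%. At a 20% response rate in both arms the effect is smaller: 4.3% with complete data, then 2.7%, 4.6% and 7.4% at 9/9, 7/11 and 5/13.

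The last column shows what the check does as a filter. At 9/9 it removes some false signals seen in completers (9.3% to 5.9%). At 5/13 it removes essentially none.

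**Distance from the real worst case.** Coding missing mifepristone as non-response and missing placebo as response gives

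bound = pt(1−dt) − [pc(1−dc) + dc].

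It lies below the protocol's procedure by exactly dc. With 9 missing per arm and observed rates of 55% and 40%, the procedure gives 0.44 − 0.32 = +12.0 points; the bound is 0.44 − 0.52 = −8.0. With 5 and 13 missing, the figures are +20.4 and −8.4.

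**The case against.** The strongest reply is that this is one label on one sensitivity analysis. The decision rule applies to the primary multiple-imputation analysis, which is unaffected. Two other procedures are planned, and the completer analysis would expose a difference created only by non-responder coding. Retention is protected: participants taken off treatment are still followed (section 4.e), a treatment adjustment does not require withdrawal (4.g), and early leavers are asked for a later clinical assessment (4.h). Section 4.p.1 also calls the results hypothesis generating. All of this stands and limits the harm. It does not make the stated property true.

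Four stronger readings are tempting, and the document does not support them:

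- **That the procedure favours mifepristone whenever placebo dropout is higher.** This is exact only with equal response rates. At 55% against 40% with 18% and 22% missing, it gives 0.55 × 0.82 − 0.40 × 0.78 = +13.9 points, still below the true 15.
- **That nothing planned tests the result against the drug.** At equal or higher mifepristone dropout this procedure does so: 15 points become 12 at 20% / 20%, and 7.25 at 25% / 15%.
- **That the chance of a false signal described as robust reaches 26%.** The 21–26% concerns this sensitivity analysis alone. The chance that it and the completer analysis both cross is about 10% at 5/13 missing. Completers serve here only as a stand-in for the within-arm imputation.
- **That the missing tipping-point analysis is itself a defect.** The statistical analysis plan is not at hand and may contain one. The error is the property the protocol asserts.

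**Conclusion.** The concern holds in limited form. For a between-arm difference, non-response coding in both arms is neither the worst case for mifepristone nor assured to be conservative. Its direction depends on dc/dt compared with pt/pc.

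Under no true effect, 40% response and 20% overall attrition, the procedure adds 4 points at 15% / 25% missing and 8 points at 10% / 30%, and with enough excess placebo dropout it stops filtering false signals. With equal dropout it is conservative, but the true bound still lies 20 points lower, which is more than the 15-point threshold.

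These sizes rest on an assumed split of attrition by arm and on missingness unrelated to outcome, and they shrink at lower response rates. The primary estimate and the decision rule are not affected. What changes is the claim of robustness that the trial could make.

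**What to change.** In section 4.p.1:

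1. Rename the first procedure non-responder imputation. Delete the worst-case label and the unqualified claim of conservatism, or state that it is conservative only if placebo missingness is not sufficiently higher than mifepristone missingness.
2. Add an analysis that goes against the drug whatever the dropout pattern. Either set missing mifepristone outcomes to non-response and missing placebo outcomes to response, or shift the imputed mifepristone week-4 CAPS scores upward in steps and report the shift at which the difference falls below 15 points.
3. Report week-4 missingness by arm next to these results.

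The cost is a small amount of programming on data already collected, with no change to sample size or conduct. The drawback is that the two-sided coding bound is deliberately extreme and will look unfavourable (−8 points in the example with 9 missing per arm). The tipping-point version is easier to interpret and may be preferred if only one is added.

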#### Secondary Outcomes:

1. The analysis specified for the one-month responder rate will also be done for the three-month responder rate as a secondary analysis to check for the sustainability of the response.

Additionally, a continuous mixed-effects model for longitudinal observations of CAPS (past week symptom status) scores (week 1, 4 and 12) will be used. Covariates including baseline characteristics, specifically duration of symptoms, duration of illness since trauma, concurrent psychotropic medication use prior to randomization, overall extent of the psychiatric co-morbidity, military cohort, and site will be explored in the adjusted analysis. This analysis will provide a treatment effect in terms of the slope of the interaction term between group and time variables, conditional on aforementioned covariates under the missing at random (MAR) assumption (Laird and Ware, 1982).

The above mentioned analyses will be performed based on a mITT principle.

2. To describe the safety and tolerability mifepristone, information on all related and unrelated SAEs will be collected. There will be accelerated safety reporting for every two adverse events in every ten participants. The specific AE(s) leading to the withdrawal of a patient from study participation will be collected, along with characteristics of the AE including severity, duration, and whether the withdrawal was at the request of the patient or was initiated by a study investigator or other clinician. The AE rate will be determined on the basis of occurrence of at least one adverse event in each participant, and the following comparisons will be carried out:
  - a. A comparison of individual adverse event rates between mifepristone and placebo.
  - b. A comparison of overall adverse event rates between mifepristone and placebo.
  - c. A comparison of severity of adverse events (grades 1, 2, 3, 4, and 5) between mifepristone and placebo
  - d. A comparison of overall adverse event rates classified as possibly or definitely attributable to study drug, between mifepristone and placebo.
  - e. A comparison of overall adverse event rates classified as possibly or definitely attributable to study drug, between mifepristone and placebo by weeks 1, 4 and 12.

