##### 1.c.2. *Secondary Objectives*

1.c.2.a. To study the trajectories of CAPS (past week symptom status) scores over the study duration for mifepristone (600 mg/day) and placebo.

1.c.2.c. To determine if a Phase III study is justified.

1.c.2.d. To compare study drug related adverse events (AEs) and serious adverse events (SAEs) in the two groups.

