### 1.d.2. Secondary Outcomes

The secondary outcome measures will be the changes in CAPS (past week symptom status) score from baseline to weeks 1, 4, and 12 to capture time by treatment interaction, the proportion of clinical responders at 12 weeks for deciding sustainability, and the percentage of study drug related AEs and SAEs to study safety and tolerability of mifepristone.

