#### 4.p. Statistical Analyses

##### 4.p.1. Analysis Plan

The randomization will be assessed by comparing the distribution of all baseline characteristics including age, race, marital status, education, duration of symptoms, duration of illness since trauma, overall extent of the psychiatric co-morbidity, whether or not on concurrent psychotropic medications and number of those medications used prior to randomization, baseline total CAPS score, military cohort, and site across the two randomized groups.

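### The named treatment effect on continuous CAPS, a group-by-time slope over weeks 1, 4 and 12, measures only change in the arm difference after dosing, so a sustained benefit gives zero

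*Protocol*

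**What the plan says.** The first secondary objective (protocol 1.c.2) is "To study the trajectories of CAPS (past week symptom status) scores over the study duration for mifepristone (600 mg/day) and placebo". The matching outcome in 1.d.2 is "changes in CAPS (past week symptom status) score from baseline to weeks 1, 4, and 12 to capture time by treatment interaction", and section 4.k repeats the three changes from baseline.

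The analysis is in 4.p.1, Secondary Outcomes, item 1. The responses are fixed first: "a continuous mixed-effects model for longitudinal observations of CAPS (past week symptom status) scores (week 1, 4 and 12) will be used". The effect measure follows: "This analysis will provide a treatment effect in terms of the slope of the interaction term between group and time variables".

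The covariates are named as "specifically duration of symptoms, duration of illness since trauma, concurrent psychotropic medication use prior to randomization", and then "overall extent of the psychiatric co-morbidity, military cohort, and site will be explored in the adjusted analysis". Baseline CAPS is not among these six. It does appear at the start of 4.p.1, in the list of characteristics compared between arms: "baseline total CAPS score, military cohort, and site across the two randomized groups".

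Section 4.e fixes treatment at one week. Section 1.b gives the rationale that a short, high-dose course may have lasting effects.

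**The concern.** Week 0 is not listed as a response, and dosing is over by week 1. Whatever the drug does between baseline and the end of dosing has therefore happened by the first modelled visit. A group-by-time slope over the three later visits ignores the level of the arm difference and picks up only its drift.

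The trial's own hypothesis is a rapid effect that lasts. On the outcome scale that is a roughly constant difference, for which the expected slope is zero. If the analysis is run and reported as worded, the quantity labelled as the treatment effect on total CAPS would miss the very pattern that the study was designed to find.

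**Working it through.** **Inputs.** Visit times 1, 4 and 12 weeks (4.p.1). Two-sided 5% tests for secondary analyses (4.p.1, closing paragraph). 90 randomised and 72 completers, so 36 per arm (4.n.2). The protocol gives no effect size, SD or power for this model, so there is no stated figure to reproduce for it. The sample size itself does reproduce: 1.2816² × (0.40×0.60 + 0.55×0.45) / 0.15² = 35.6, or 36 per arm, and 72/0.8 = 90.

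**Formula.** With balanced, complete data and a random intercept, the group-by-linear-time coefficient is the least-squares slope of the arm difference d(t) on t:

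slope = Σ(t − t̄)d(t) / Σ(t − t̄)²

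Here t̄ = 17/3 = 5.667. The deviations are -4.667, -1.667 and 6.333, and their sum of squares is 21.78 + 2.78 + 40.11 = 64.67.

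**Results.** Differences are mifepristone minus placebo, negative meaning benefit. The first three profiles are assumed.

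| Pattern | Weeks 1, 4, 12 | Numerator | Slope per week |
|---|---|---|---|
| Sustained | -10, -10, -10 | 0 | 0 |
| Fading | -15, -10, -5 | 70.0 + 16.7 − 31.7 = 55.0 | +0.85 |
| Growing | -5, -10, -15 | 23.3 + 16.7 − 95.0 = −55.0 | -0.85 |
| Pilot, held flat after week 4 | -13.00, -21.25, -21.25 | 60.7 + 35.4 − 134.6 = −38.5 | -0.60 |

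The week-4 difference is the same, -10, in the first three rows. The deviations sum to zero, so any constant difference gives slope 0. The pilot row uses the Table 1 means (43.50 − 56.50 at endpoint and 44.00 − 65.25 at four weeks). Its week-12 value is an assumption.

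**Do simple changes of reading repair it?**
- *Change from baseline as the response.* Each participant's baseline is subtracted equally at all three visits, so the slope does not move.
- *Baseline CAPS as a covariate.* With complete data this shifts levels, not the slope.
- *Week 0 added as a response, time still linear.* Now t̄ = 4.25 and the sum of squares is 88.75. The sustained profile gives −42.5/88.75 = -0.48 per week, but the fading profile still gives +12.5/88.75 = +0.14. This is only a partial repair.
- *Week as categories.* With week 1 as reference, the interaction terms for weeks 4 and 12 are 0 and 0 for the sustained profile, and +5 and +10 for the fading one. The visit differences can be recovered by adding the group term, but the interaction alone still does not show them.

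**Illustration of size.** In 4,000 simulated trials with 36 per arm (assumed SD 15 at baseline and 20 afterwards, all correlations 0.6, complete data):
- Sustained 12-point benefit: the slope test rejected in 5.5% of trials, against 5.4% with no effect. The baseline-adjusted average difference was -11.9 and was detected in 98%.
- Fading benefit (-16, -12, -4): the slope averaged +1.07 per week and was significant with a positive sign in 82%. The adjusted average difference was -10.7 and was detected in 95%.

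The percentages depend on these assumptions. The zero and the sign do not.

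**The case against.** The stated objective is trajectories, and section 1.d.2 itself speaks of a time-by-treatment interaction. A positive slope after week 1 is a correct description of arms converging, and fitted means from the same model would still show mifepristone lower at each visit. Durability is also examined through the three-month responder rate. The coding of time is not stated and could be settled in an analysis plan that is not shown. The pilot difference grew from endpoint to week 4, a pattern for which the slope has the right sign. The results are declared hypothesis-generating.

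Most of this stands, and it limits the point. It does not remove it. The protocol does not merely report an interaction: it names that slope as the treatment effect. Sections 1.d.2 and 4.k define the outcome as change from baseline to each visit, and the slope estimates the arm difference in none of those changes. The responder rate at three months is a different, dichotomised measure. The pilot had four participants per arm and no week-12 value in Table 1.

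A second CAPS mixed model does exist (4.p.1, Descriptive Outcomes, item 8c), with an arm indicator, so it would be wrong to say that item 1 is the only one. But item 8c also adjusts for week-1 plasma drug levels, which are a consequence of treatment. Its arm term cannot serve as the overall treatment effect.

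**Conclusion.** The point holds for sustained and fading benefits, with time read as linear. The named effect is exactly 0 for a constant difference of any size, and +0.85 points per week for differences of -15, -10 and -5. For a benefit that grows after week 1 the sign is right, although the slope still does not give the size of the difference at any visit. The profiles are assumed because the protocol offers none for this model.

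Two stronger readings are tempting, and the document does not support them:
- A reader might infer that the plan would declare a fading benefit to be harm. It would not have to: the slope would be positive, but that correctly describes convergence. The fault is in calling it the treatment effect.
- A reader might infer that leaving baseline CAPS out of the covariates causes the zero or reversed slope. It does not. The omission is a separate and smaller matter: it costs precision and leaves chance imbalance in any comparison of levels. The wording, which has covariates explored rather than fixed, leaves some room to add it.

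The primary responder rule and the sample size are untouched. This should be fixed, but it is not critical.

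**What to change.** In 4.p.1, Secondary Outcomes, item 1, respecify the model for CAPS at weeks 1, 4 and 12 with treatment, week as a categorical factor, treatment-by-week terms and baseline CAPS as a covariate. Define the treatment effect as the baseline-adjusted mean difference at week 4, and report the adjusted differences at weeks 1 and 12 beside it. Keep the interaction as the description of trajectory, for example as the week-12 minus week-4 contrast. This ties the analysis to the outcome in 1.d.2 and 4.k and still answers the objective in 1.c.2.

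The cost is a short change of text and a few more model parameters. All the variables are already collected at the scheduled visits.
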